## Efficacy endpoints

- Proportion of patients with any parasitemia on day 1, 2 and 3 after treatment
- Proportion of patients with fever on day 1, 2 and 3 after treatment
- Recurrence of parasitaemia within 30 days of follow up
- Proportion of Pf patients with gametocytemia on any of the follow up dates.

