# Laboratory and test procedures

## Microscopy

Slides for microscopy will be collected upon enrolment and on all follow up days as well as on any unscheduled visit days.

All slides collected between day 0 and day3 will be re-read by an expert microscopists. Blood smears with discordant results (differences between the two microscopists regarding species diagnosis, parasite density of > 50% or regarding the positivity in general) will be re-examined by a third, independent microscopist, and parasite density will be calculated by averaging the two closest counts.

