# Data Management

Data will be entered into a custom-made database. Internal error checks and systematic error assessment will be developed to check for data entry discrepancies, invalid data ranges and overall consistency. All discrepancies will be resolved by reference to the original data collection forms.

Original data collection forms will be handled only by staff members and kept under locked storage until completely coded, checked and transported for data entry. Once data entry and cleaning are complete the original forms will be stored as long as required by national laws.

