# Sample Size

In 2013 a total of 142 vivax cases and 2190 falciparum cases were registered within the district of Alikadam with the majority of cases occurring during and after the monsoon season. The study hospital treated a total of 49 vivax cases and 432 falciparum cases in the same year. As the proposed study will be conducted during the peak malaria season we propose an enrolment target of approximately 50 vivax cases and 160 falciparum cases.

This study is part of a framework of comparable studies working with similar tools as proposed herein. Results for the primary objective will be pooled together with results of other sites to provide reliable results.

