**17. G6PD result:** ☐☐.☐ **IU/g Hb**

18. **Schizontocidal Treatment**

| Schizontocidal treatment | Pf | Pv | mixed |
| --- | --- | --- | --- |
| 1^st^ Dose (observed) | AL given  ☐ Yes ☐ No ☐  Dose:___________ | CQ given  ☐ Yes ☐ No ☐  Dose:___________ | AL given  ☐ Yes ☐ No ☐  Dose:___________ |
| 2^nd^ Dose | AL given  ☐ Yes ☐ No ☐  Dose:___________ | N/A | AL given  ☐ Yes ☐ No ☐  Dose:___________ |
|  | Was this dose given as observed treatment  ☐yes ☐no |  | Was this dose given as observed treatment  ☐yes ☐no |

19. **Primaquine treatment**

| Primaquine treatment | Pf | Pv | mixed |
| --- | --- | --- | --- |
|  | PQ single dose provided tp patient  ☐ Yes ☐ No ☐  Dose:___________ | PQ full course provided to patient  ☐ Yes ☐ No ☐  Dose:___________ | PQ full course provided to patient  ☐ Yes ☐ No ☐  Dose:___________ |

**Day – 6: Date of visit:** ☐☐-☐☐-☐☐☐☐

20. **Temperature:** ☐☐.☐˚C

21. **Finger prick collected?** ☐ Yes ☐ No

*If yes:* **Blood slide collected?** ☐ Yes ☐ No

*If yes:* Time: ☐☐:☐☐ in 24:00 format (e.g. 4pm is 16:00)

**Parasite count** ________/500RBC or ___________/200WBC

Diagnosis: ☐ Pf ☐ Pv ☐Mixed ☐neg

*If yes:* **Hemoglobin measured?** ☐ Yes ☐ No

*if Yes:* ☐☐.☐ g/dl

**Day – 9: Date of visit:** ☐☐-☐☐-☐☐☐☐

22. **Temperature:** ☐☐.☐˚C

23. **Finger prick collected?** ☐ Yes ☐ No

*If yes:* **Blood slide collected?** ☐ Yes ☐ No

*If yes:* Time: ☐☐:☐☐ in 24:00 format (e.g. 4pm is 16:00)

**Parasite count:** ________/500RBC or ___________/200WBC

Diagnosis: ☐ Pf ☐ Pv ☐Mixed ☐neg

*If yes:* **Hemoglobin measured?** ☐ Yes ☐ No

*if Yes:* ☐☐.☐ g/dl

**Day – 12: Date of visit:** ☐☐-☐☐-☐☐☐☐

24. **Temperature:** ☐☐.☐˚C

25. **Finger prick collected?** ☐ Yes ☐ No

*If yes:* **Blood slide collected?** ☐ Yes ☐ No

*If yes:* Time: ☐☐:☐☐ in 24:00 format (e.g. 4pm is 16:00)

**Parasite count :** ________/500RBC or ___________/200WBC

Diagnosis: ☐ Pf ☐ Pv ☐Mixed ☐neg

*If yes:* **Hemoglobin measured?** ☐ Yes ☐ No

*if Yes:* ☐☐.☐ g/dl

**Day – 16: Date of visit:** ☐☐-☐☐-☐☐☐☐

26. **Temperature:** ☐☐.☐˚C

27. **Finger prick collected?** ☐ Yes ☐ No

*If yes:* **Blood slide collected?** ☐ Yes ☐ No

*If yes:* Time: ☐☐:☐☐ in 24:00 format (e.g. 4pm is 16:00)

**Parasite count :** ________/500RBC or ___________/200WBC

Diagnosis: ☐ Pf ☐ Pv ☐Mixed ☐neg

*If yes:* **Hemoglobin measured?** ☐ Yes ☐ No

*if Yes:* ☐☐.☐ g/dl

28. **Meth hemoglobin measured (only Pf/Pv and Pv patients > 2 years)?** ☐ Yes ☐ No

*if Yes:* ☐☐.☐ in %

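### Gametocytaemia in falciparum patients is an efficacy endpoint, but neither the annexed case record form nor the microscopy section provides for gametocytes to be read or recorded

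*Protocol*

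**What the plan says.** Section 5.2 of the Protocol (Efficacy endpoints) lists "Proportion of Pf patients with gametocytemia on any of the follow up dates". The synopsis list of efficacy endpoints omits it.

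Section 4.5.1 (Microscopy) provides the slides: "Slides for microscopy will be collected upon enrolment and on all follow up days as well as on any unscheduled visit days". It also plans a second read for part of the follow-up: "All slides collected between day 0 and day3 will be re-read by an expert microscopists". Two reads are discordant if they differ on species, density or positivity. After a third read, "parasite density will be calculated by averaging the two closest counts". Parasite stage is not mentioned.

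The case record form (Annex IX) takes a parasite count per slide in the format "500RBC or ___________/200WBC". From day 6 it adds a tick-box line: "Diagnosis: ☐ Pf ☐ Pv ☐Mixed ☐neg". Day 0 has a similar line without the negative option.

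Under Data Management, the forms are the reference for the database: "All discrepancies will be resolved by reference to the original data collection forms".

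**The concern.** An endpoint needs a planned observation and a place to record it. Here the slides are planned, but nobody is told to look for gametocytes and the form has no box for them. A nonzero count or a falciparum tick does not say which stage was seen, so neither can stand in for the endpoint.

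Two things are at stake:

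- The Background (section 1.1) gives gametocidal action as primaquine's property in falciparum malaria. This is the only listed efficacy endpoint that measures that action directly. Carriage on day 0 is not recorded either. The endpoint as worded does not require it, but without it later carriage cannot be separated into persisting and new.
- The same undifferentiated count feeds other efficacy results: any parasitaemia on days 1, 2 and 3, recurrence within 30 days, and time to the first negative slide. A slide with gametocytes only cannot be told on the record from one with asexual parasites.

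**Working it through.** The Protocol attaches no figure to this endpoint, so there is none to reproduce. The check is a count of fields and a comparison of sections.

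**Slide-result fields in Annex IX**

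| Form page | Parasite-count fields | Species-diagnosis fields | Fields for gametocytes or stage |
|---|---|---|---|
| Day 0 (two slides) | 2 | 2 | 0 |
| Day 1 (two slides) | 2 | 0 | 0 |
| Day 2 (two slides) | 2 | 0 | 0 |
| Days 6, 9, 12, 16, 23, 30 (one each) | 6 | 6 | 0 |
| Unscheduled visits 1 and 2 (one each) | 2 | 2 | 0 |
| Total | 14 | 10 | 0 |

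Counts: 2 + 2 + 2 + 6 + 2 = 14. Diagnoses: 2 + 6 + 2 = 10. The symptom, concomitant-medication and end-of-study pages contain no gametocyte item either.

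**Other places that could fill the gap**

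- Microscopy (section 4.5.1): gives no instruction to read or report gametocytes.
- Treatment and follow-up schedule table: lists microscopy, with nothing on stage.
- Statistical analyses (section 7): does not mention gametocytes.
- Objectives (section 3): none concerns gametocytes or transmission.
- Background (section 1.1): refers to gametocidal properties only as a property of the drug.

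**Patients concerned.** Under Sample Size, "we propose an enrolment target of approximately 50 vivax cases and 160 falciparum cases". The denominator is falciparum patients, so about 160 have no recorded numerator value on any visit.

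**Could the planned second read supply the data?** Falciparum patients take primaquine on day 3 (section 4.4.1, Annex V). The expert re-read stops at day 3, so every slide it covers precedes the dose or falls on the dosing day. Later slides, which would show a gametocidal effect, have only the routine read. Stage is not among the grounds for discordance at any time point.

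**The case against.** The strongest reply is that the data source is the slide, and slides are taken at enrolment and at every follow-up and unscheduled visit. What is missing is a box for the result. Several other planned results also have no box on the form: the rapid test, the second and third slide reads, serology, flow cytometry, parasite genotyping, G6PD variants and the pregnancy test. Some results must therefore be kept elsewhere, and gametocyte reads might be too.

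Part of this stands. A reader might infer that the endpoint can never be scored, or that its data are lost for every falciparum patient. The documents do not support that, because stored slides could be read again. The comparison with the other tests does not close the gap, however. Those procedures are at least named or described in the Protocol, whereas reading slides for gametocytes is described nowhere.

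A second reply concerns importance. The endpoint is descriptive, there is no randomised comparison, and no objective rests on it. That is correct. A reader might also infer that nothing else could show what the single primaquine dose does in falciparum patients. This goes too far: the haemoglobin, transfusion and adverse-event endpoints cover those patients and address the primary objective. Nor is the falciparum share of planned enrolment, 160/(50 + 160) = 76%, a measure of harm. It describes the case mix, while this endpoint is defined in falciparum patients only.

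Finally, an SAP may define how a variable is analysed, but it cannot supply one that the annexed form does not collect.

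**Conclusion.** The point holds as a mismatch between a listed efficacy endpoint and the planned data capture. None of the 14 count fields or 10 diagnosis fields identifies gametocytes, and no section asks for them to be read. Followed as written, the plan yields no data for this endpoint in about 160 falciparum patients, although an unplanned re-reading of slides could recover it. The primary safety objective is unaffected. The side effect on the parasitaemia, clearance and recurrence results is an ambiguity of unknown size, because the Protocol gives no gametocyte carriage rate.

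The conclusion assumes that the annexed form is complete. Nothing in it suggests that a separate laboratory results page exists. The point should be corrected because the repair is cheap during the study and laborious afterwards.

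**What to change.** 1. Add a gametocyte field (presence and count) to every slide record in Annex IX, including day 0 and the unscheduled visits.
2. State that the existing parasite-count field means asexual parasites, and use that meaning in the parasitaemia, clearance and recurrence endpoints.
3. Add to the microscopy section that all slides, including those after day 3, are read for gametocytes at the routine read. Extending only the day 0 to 3 expert re-read would not cover the slides taken after the dosing day.
4. Add the endpoint to the synopsis. If the sponsor does not want to collect it, delete it from section 5.2 instead.

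In the same edit, settle which dates count as follow-up for falciparum patients. The schedule table's falciparum row marks day 12 and not day 9, while the text of Study Procedures gives day 9. These passages must be reconciled.

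The cost is one form line per slide and slightly longer reading of slides that are already made and read. No extra visit or blood sample is needed.

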## Other Endpoints

- Proportion of patients adhering to 14 days of primaquine treatment in the vivax cohort as measured by Masimo and pill count
- Distribution of G6PD activity among the study population
- Frequency and type of variants of the G6PD gene within the study population

# Data Management

Data will be entered into a custom-made database. Internal error checks and systematic error assessment will be developed to check for data entry discrepancies, invalid data ranges and overall consistency. All discrepancies will be resolved by reference to the original data collection forms.

Original data collection forms will be handled only by staff members and kept under locked storage until completely coded, checked and transported for data entry. Once data entry and cleaning are complete the original forms will be stored as long as required by national laws.

# Statistical analyses

- Safety data will be presented as summary statistics (including number, mean, median, interquartile range, standard deviation, minimum and maximum) of all vital signs variables (values and changes from baseline) will be calculated for each visit by treatment group.
- G6PD activity will be categorised and the relative risk (RR) of a drop of Hb > 25% between day 3 and 9 and day 3 and 16 and day 23 and 30 will be calculated per category for all participants treated with 14 days of PQ.
- Hematological results will be presented as continuous variable of Hb concentration at Day 0, 3, 6, 9, 12 and 16. The fractional fall in Hb between baseline and day 9 and 16, will be calculated, as well as the proportion of patients with anaemia less than 7g/dl between day 3 and day 9.
- Parasite clearance rate will be defined according to the World Wide Antimalarial Resistance Network guidelines (WWARN)[[20](#_ENREF_20)]. The parasite clearance time (PCT) is defined as the time elapsed between the patient’s first dose and the time of the first negative blood slide.
- G6PD variants detected will be presented descriptively, G6PD activity observed will be displayed in the form of a histogram displaying G6PD activity vs. number of patients.

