## Rationale and Aim

Unpublished data on the prevalence of G6PD deficiency in Bangladesh indicate rates of 20-40% in the local population. Current national guidelines recommend the addition of Primaquine to antimalarial treatment for *P. falciparum* (single dose treatment) and *P. vivax* mono- infections (14days treatment) as well as for *P. falciparum / P. vivax* mixed infections (14 days treatment). In view of lack of available reliable bedside testing primaquine is administered without prior testing of G6PD status. This study aims to assess possible side effects as a result of current national malaria treatment guidelines. To do so we propose an observational study to assess current national treatment guidelines for vivax and falciparum malaria, considering both host and parasite factors that may influence treatment effectiveness.

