**Secondary:**

- To assess the schizontocidal efficacy of 3 days chloroquine (CQ) for *P. vivax*
- To assess parasite clearance rates in P*. falciparum* patients treated with artemether-lumefantrine (AL)
- To determine the risk of haemolysis associated with G6PD activity
- To determine the distribution of G6PD activity and genetic variants among malaria patients
- To determine parasite related factors that may affect treatment outcome

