## Exclusion Criteria

- Bodyweight <6kg
- Presence of general danger signs in children aged under 5 years or signs of severe malaria according to the definitions of WHO (Annex III)
- Presence of severe malnutrition^[[1]](#footnote-1)^
- Acute anaemia <8g/dL
- Regular medication, which may interfere with antimalarial pharmacokinetics
- History of hypersensitivity reactions or contraindications to any of the drug(s) tested or used as alternative treatment(s)
- A positive pregnancy test or lactating.
- Severe G6PD deficient patients will be excluded from PQ treatment

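### By G6PD category the protocol states only a relative risk of a >25% Hb fall, which has no value if the 30-50 or so G6PD-normal patients have no event

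*Protocol*

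**What the plan says.** One secondary objective is "To determine the risk of haemolysis associated with G6PD activity". The Statistical analyses section serves it with a single item. It puts G6PD activity into categories and plans "the relative risk (RR) of a drop of Hb > 25% between day 3 and 9", and likewise for days 3 to 16 and days 23 to 30. The result "will be calculated per category for all participants treated with 14 days of PQ". That population is the vivax and the mixed-infection patients. The section states no risk per category and no risk difference.

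Other measures of haemolysis are stated for the cohort. The Safety endpoints section lists severe anaemia, transfusion, fractional Hb change and the proportion with a fall above 25%. The Statistical analyses section adds Hb as a continuous variable. None of these is stated by G6PD category.

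On numbers, the Sample Size section says "we propose an enrolment target of approximately 50 vivax cases and 160 falciparum cases". It gives no target for mixed infections and promises pooling across sites for the primary objective only. On G6PD status, the Rationale and Aim section says that unpublished data "indicate rates of 20-40% in the local population". The Exclusion Criteria add: "Severe G6PD deficient patients will be excluded from PQ treatment".

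**The concern.** A relative risk divides by the risk in a reference group. The natural reference here is the normal-activity category, which holds a few dozen patients. If none of them has a fall above 25% in a window, the RR for that window has no value. If the other category has no event either, it is 0/0.

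The study asks whether primaquine given without G6PD testing causes harm. The clearest possible signal would be several large falls among deficient patients and none among normal patients. That is exactly the result for which the stated measure gives no point estimate. The absolute excess of patients with a large fall, which bears directly on a treatment guideline, could still be estimated but is not a stated result by category.

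**Working it through.** **Plan's own figure.** There is none to reproduce. The protocol states no power, precision or event rate, and the 50 and 160 are based on case load.

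**Inputs**
- 14-day primaquine group: about 50 vivax patients (Sample Size).
- Mixed infections: no target is given. At the 2013 Alikadam ratio of 26 mixed to 142 vivax (table under Study Site), 50 × 26/142 ≈ 9.
- G6PD deficiency: 20-40% (Rationale and Aim). The normal group is then n = 50 × 0.80 = 40 or 50 × 0.60 = 30. If none of the 50 is deficient, n = 50.
- Risk p of a >25% fall in a normal patient in one window: not in the protocol. Assumed values of 1% to 10% are shown.

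**Chance of no event among n normal patients = (1 − p)^n**

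| Assumed p | n = 30 | n = 40 | n = 50 |
| --- | --- | --- | --- |
| 1% | 0.99^30 = 74.0% | 0.99^40 = 66.9% | 0.99^50 = 60.5% |
| 2% | 0.98^30 = 54.6% | 0.98^40 = 44.6% | 0.98^50 = 36.4% |
| 5% | 0.95^30 = 21.5% | 0.95^40 = 12.9% | 0.95^50 = 7.7% |
| 10% | 0.90^30 = 4.2% | 0.90^40 = 1.5% | 0.90^50 = 0.5% |

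**Sensitivity of the group size**
- With 9 mixed cases added (59 patients, n = 35 to 47), the chance is 70% to 62% at p = 1% and 17% to 9% at p = 5%.
- With an assumed 10-20% loss to follow-up from the 50 (n = 24 to 36), it is 79% to 70% at 1% and 29% to 16% at 5%.

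**Chance of no event in normal patients and at least one in deficient patients.** Assume a 30% risk in the deficient.
- 40 normal and 10 deficient: 0.669 × (1 − 0.7^10) = 65% at p = 1%; 0.1285 × (1 − 0.7^10) = 12% at p = 5%.
- 30 normal and 20 deficient: 74% and 21%.

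**What each measure gives in two illustrative results**
- *3/10 against 0/40.* RR = 0.30/0 is undefined. The risk difference is 30 points. The Wilson limits are 0.108 to 0.603 for 3/10 and 0 to 0.088 for 0/40. Newcombe lower limit: 0.30 − √[(0.300 − 0.108)² + (0.088 − 0)²] ≈ 0.09. Upper limit: 0.30 + √[(0.603 − 0.300)² + 0²] ≈ 0.60. The 95% CI is about 9 to 60 points.
- *3/10 against 1/40.* RR = 0.300/0.025 = 12. SE of log RR = √(1/3 − 1/10 + 1/1 − 1/40) = 1.10, so the 95% CI is about 1.4 to 103. The risk difference is 27.5 points. With Wilson limits of 0.004 to 0.129 for 1/40, the Newcombe 95% CI is about 6 to 58 points.

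**The case against.** The strongest reply is that this is a routine zero cell, which a statistical analysis plan would handle. An RR cannot be calculated without the category proportions, so those will be known. With 3/10 against 0/40, Fisher's exact test gives p = 120/19,600 = 0.006, and exact or score methods give a finite lower limit for the RR. The RR is also a standard cohort measure for a secondary objective. Much of this stands. Only the point estimate of the RR is lost, and a reader who inferred that the study would have no result on haemolysis would go too far. The choice of a ratio as the measure by G6PD category, however, is made in the protocol itself.

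Other stronger readings are tempting but not supported:
- **That the RR is the protocol's only measure of haemolysis.** The Safety endpoints and Statistical analyses sections state several cohort-level measures. The point is confined to haemolysis by G6PD category.
- **That a chance of 13-74% follows from the planned size.** That range needs an assumed risk of 1-5% in normal patients. At 10% it is 2-4%.
- **That the normal group is surely 30-40.** The 20-40% refers to the local population. The background section on local epidemiology calls deficiency protective against vivax infection, severely deficient patients receive no primaquine, and mixed infections are included. The normal group may therefore be larger.
- **That the missing reference category is an error.** Category limits, the reference and zero-cell rules can properly be left to an analysis plan, and one may exist.
- **That the wide interval condemns the RR.** The width comes from the sample size; the risk difference is imprecise too.

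**Conclusion.** The point holds in a limited form. The one measure that the protocol ties to G6PD category can lack a value when the normal group has no event. With 30-40 normal patients that is likely if their true risk is about 1-2% (45-74%), still realistic at 5% (13-21%) and unlikely at 10% (2-4%). With 50 normal patients it is about 61% at 1% and 8% at 5%. All these chances rest on event risks that the protocol does not give, and on the normal-activity category as reference, which is a natural reading but not a stated one.

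Pooling is no safeguard, because it is promised only for the primary objective and this objective is secondary. The consequence is a gap in the stated result for one secondary objective. It does not invalidate the study.

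**What to change.** Add one sentence to the Statistical analyses section. For each G6PD category and each window, report the number and proportion with a >25% Hb fall with an exact 95% CI, and the risk difference against the normal-activity category with a Newcombe or exact unconditional CI. Keep the RR as an additional measure where it can be estimated.

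The cost is that sentence and a little more analysis work, with no added patients, visits or samples. The change gives an estimate whenever each category contains patients. It does not make a sample of this size more precise, and the report should say so.

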# Objective

**Primary:**

- To assess side effects observed following unsupervised PQ treatment in *P. vivax* and *P. falciparum* patients

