### Treatment & sample collection

Patients will receive the following treatment according to national guidelines (Annex II, IV and V) and will be asked to return for follow up:

- **Vivax patients**

CQ (Annex IV) will be administered for three days under direct observation. All patients will be observed for 30 min after drug administration for adverse reactions or vomiting. Any patient who vomits during this observational period will be re-treated with the same dose and observed for an additional 30 min. If the patient vomits the study drug a second time, he or she will receive rescue therapy as defined by the national treatment guidelines (Annex VI).

PQ (Annex V) will be administered unsupervised for 14 days from day 3 – 16.The complete treatment course of PQ will be provided to the patients after completion of schizontocidal treatment. All patients will receive instructions on how to take the drugs and will be asked to return for follow up on, day 6, day 9, day 12, day 16 (at the end of treatment), day 23 and day 30, as well as whenever the patients suffers from signs and symptoms consistent with malaria or an adverse reaction to one of the study drugs. (Annex IX).

- **Falciparum patients:**

AL will be administered twice daily for three days (Annex III). The morning dose will be supervised and the patients given tablets for the evening dose. Whenever supervised treatment is administered, the study patients will be observed for 30 min after drug administration for adverse reactions or vomiting. Any patient who vomits during this observational period will be re-treated with the same dose of medicine and observed for an additional 30 min. If the patient vomits the study drug a second time, he or she will receive rescue therapy (Annex VI). PQ will be given to the patients after schizontocidal treatment is finished and the patients are advised to take the single dose (Annex V) on day 3 unsupervised. All patients will be asked to return for follow up on day 9, day 16, day 23, day 30 and whenever participants suffer from signs and symptoms consistent with malaria or an adverse reaction to one of the study drugs within the follow up period (Annex IX).

- **Patients with mixed infection (Pf and PV):**

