## Enzyme activity testing

G6PD activity will be measured using spectrophotometry at the lab maintained by icddr,b for all participants. Samples are transported on a daily basis from the field to the icddr,b lab and results are communicated to the field. A subset of collected samples, tested with spectrophotometry, will be tested with flow cytometry to assess lyonisation at a reference centre capable of performing the respective procedure

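### The haemolysis-by-G6PD objective has no species or regimen limit, but its only stated analysis leaves out the single-dose falciparum patients, about three quarters of the target enrolment

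*Protocol*

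**What the plan says.** The primary objective is "To assess side effects observed following unsupervised PQ treatment in" vivax and falciparum patients. A separate secondary objective reads "To determine the risk of haemolysis associated with G6PD activity", with no species and no regimen attached.

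The Protocol, Statistical analyses, turns the second into one calculation. G6PD activity is put into categories, and the plan computes a relative risk of losing more than a quarter of Hb over three windows: days 3 to 9, days 3 to 16, and days 23 to 30. The population is fixed in the same sentence: the figure "will be calculated per category for all participants treated with 14 days of PQ". By the Study Procedures, 14 days of PQ means vivax and mixed infections.

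For falciparum patients, Treatment & sample collection states that "the patients are advised to take the single dose (Annex V) on day 3 unsupervised". Enzyme activity testing states that "G6PD activity will be measured using spectrophotometry at the lab maintained by icddr,b for all participants". The Hemoglobin section plans Hb at baseline and at every follow-up visit. Sample Size gives the target: "we propose an enrolment target of approximately 50 vivax cases and 160 falciparum cases".

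The other haematology item in Statistical analyses (Hb by day, fractional fall to days 9 and 16, anaemia) is not broken down by G6PD category. The remaining G6PD items are a description of variants and a histogram of activity.

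**The concern.** The objective asks about haemolysis across G6PD activity without limit, and the analysis answers it for one of the two PQ regimens without giving a reason. The Protocol's rationale is that PQ is given untested in a population with 20-40% G6PD deficiency, under a guideline that includes the falciparum single dose. Most patients treated under that guideline at this site have falciparum malaria. If the plan is followed as written, the study will hold a G6PD value and serial Hb for each single-dose patient and still not report whether Hb fall varies with G6PD activity after that dose.

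**Working it through.** **Share of the cohort left out.** From Sample Size: 160/(50 + 160) = 76.2%. Mixed infections have no target. The 2013 table gives Alikadam 142 vivax and 26 mixed cases, so 50 × 26/142 ≈ 9 mixed patients might join the 14-day group. The share is then 160/219 = 73%, and the 14-day group is about 59.

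**Which Hb windows exist for falciparum patients.**

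| Visit | Text (Study Procedures; Treatment & sample collection) | Schedule table |
|---|---|---|
| Day 9 | falciparum visit | not in the falciparum follow-up row |
| Day 12 | vivax and mixed only | in the falciparum follow-up row |
| Day 16 | falciparum visit | in the falciparum follow-up row |
| Days 23 and 30 | falciparum visits; the Hemoglobin section implies Hb | visits, but Hb marked for vivax and mixed only |

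Day 16 is the only visit up to the end of the 14-day course that both sources give to falciparum patients after PQ. Day 3 is bracketed in the table and has no page in the case record form, so the last Hb before PQ will often be that of day 2.

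**Precision.** The Protocol gives no event rate or power figure, so there is none to reproduce. For illustration I assume that 30% of patients fall in a lower-activity category (the middle of the Protocol's 20-40%) and a relative risk (RR) of 4.

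SE(log RR) = √[(1 − p1)/(n1·p1) + (1 − p0)/(n0·p0)]; 95% interval = 4 × exp(±1.96 × SE); chance of no event in the reference category = (1 − p0)^n0.

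- *Falciparum, 48 vs 112, risks 20% vs 5%:* √(0.80/9.6 + 0.95/5.6) = √0.253 = 0.50. Interval about 1.5 to 11. Empty reference: 0.95^112 = 0.3%.
- *Falciparum, 48 vs 112, risks 4% vs 1%:* √(0.96/1.92 + 0.99/1.12) = √1.384 = 1.18. Interval about 0.4 to 40. Empty reference: 0.99^112 = 32%.
- *14-day group, 15 vs 35, risks 20% vs 5%:* √(0.80/3 + 0.95/1.75) = √0.810 = 0.90. Interval about 0.7 to 23. Empty reference: 0.95^35 = 17%.

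At 20% vs 5% the share deficient matters little. With 20% or 40% deficient, the SE is 0.52 or 0.51 in the falciparum group and 0.94 or 0.91 in the 14-day group. The formula is rough at 4% vs 1%, where only 1.92 and 1.12 events are expected. Severely deficient patients do not receive PQ, so the number of deficient patients exposed would be lower than assumed in both groups.

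**Exposure.** Annex V, tablets per weight band: the single falciparum dose (1/2 to 3) exceeds the daily vivax dose (1/4 to 1) in every band. The 14-day total (14 × 1/4 = 3.5, up to 14 × 1 = 14) exceeds the single dose by a factor of 14/3 = 4.7 to 14/1.5 = 9.3. Neither regimen stands in for the other.

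**The case against.** The strongest reply is that the restriction is a reasonable way to make a broad objective operational. The 14-day course gives several times the cumulative dose, one relative risk over both regimens would be hard to interpret, and an extra table by G6PD category is something a statistical analysis plan could add. The first two points stand, but they argue for keeping the regimens apart, not for leaving one out. The third is weaker, because the Protocol is not silent here: it names the population and gives no reason for it. Pooling across sites does not fill the gap either, since Sample Size promises it for the primary objective only.

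A reader might infer more than the Protocol supports:

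- *That an objective asks about haemolysis in both species.* None does. The primary objective names both species but speaks of side effects; the haemolysis objective names neither.
- *That falciparum Hb data are ignored.* They are not. Fractional Hb change, drops above 25%, severe anaemia, transfusion and adverse events have no species limit under Safety endpoints. Only the link to G6PD activity is missing.
- *That the falciparum group would give a clear answer where the 14-day group cannot.* That holds only if one dose carries the same risks as fourteen. At 4% vs 1%, the falciparum interval is wider than the 14-day interval at 20% vs 5%.
- *That the single dose is the greater exposure.* It is larger per intake and smaller in total.

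**Conclusion.** The point holds as an unexplained mismatch between an unrestricted secondary objective and a narrower analysis population. It leaves about 160 of 210 targeted patients (76%; about 73% with mixed cases at the 2013 ratio) outside the only stated analysis of Hb fall by G6PD activity, although they take PQ and both measurements are planned. The 14-day analysis itself remains valid, and the primary objective is unaffected.

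How much the missing analysis could show is unknown. Under the stated assumptions the interval around a relative risk of 4 runs from about 1.5 to 11 down to about 0.4 to 40, depending on the single-dose risk. That supports reporting an estimate with its interval, not promising a test.

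**What to change.** In Statistical analyses, add a separate analysis of Hb fall by G6PD category among falciparum patients who received the single dose, not pooled with the 14-day regimen.

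- **Window:** from the last Hb before PQ to day 16. Add day 9 once the text (day 9) and the falciparum row of the schedule table (day 12) have been reconciled.
- **Not days 23-30** for this group, unless the schedule table (Hb in vivax and mixed only) and the Hemoglobin section (Hb at all follow-up visits) are reconciled.
- **Reporting:** the estimate with its confidence interval, using the same G6PD categories as in the 14-day group.

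The cost is one extra table from measurements already planned, and more comparisons to report. If the investigators do not want this analysis, one sentence limiting the objective to 14-day PQ, with the reason, would remove the mismatch but leave the single-dose question open. Neither change narrows the interval in the 14-day group; that is a matter of its size.
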